**Discussion:**

The PROMOTE trial is designed to examine whether MTX is an effective analgesic treatment for OA. The MRI substudy will address the relationship between synovitis and symptom change. This will potentially provide a much needed new treatment for knee OA.

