### Trial objectives

The primary objective of the trial is to determine whether MTX reduces pain associated with knee OA as compared to placebo. Secondary objectives of the trial are:To determine whether MTX improves function,To determine whether MTX improves quality of life andTo determine whether MTX is a cost-effective treatment for knee OA.

In addition to the main study, PROMOTE contains a magnetic resonance imaging (MRI) substudy and a biological substudy. Patients enrolled in the main study may opt to enrol in one, both or neither of the sub-studies. The objective of the MRI substudy is to provide an explanatory mechanism for associated symptom change by examining whether MTX reduces synovitis, and whether this is related to symptom change. The objective of the biological substudy is to determine whether baseline soluble immunological and inflammatory biomarkers predict response to treatment, and whether changes in levels occur following treatment with MTX.

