Adverse events will be coded according to the MedDRA adverse event dictionary. The overall incidence of serious adverse events and adverse events and number and proportion of patients reporting such events will be summarized by treatment group. Adverse events (including serious adverse events) will be summarized by the number and percentage of subjects who experienced the event by system organ class and preferred term. Subjects will only be counted once. If a subject reports the same adverse event more than once then the maximum grade and strongest causal relationship to study treatment will be used for the summary tables. Adverse events will also be summarized by severity and by relationship to study drug. All adverse events will be included in individual subject line listings.

Analysis of MRI endpoints will be exploratory. Treatment groups will be compared with respect to changes in synovitis, cartilage and bone using linear regression models with adjustment for the same covariates as the primary analysis. Linear regression models will also be used to explore the association between symptom outcome and baseline MRI measurements. Changes in MR features and the relationship of these changes with symptom changes will be explored descriptively.

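### MRI substudy: the link between synovitis change and symptom change is only described, with no arm-adjusted estimate, and the covariate wording does not clearly include each MRI feature's own baseline

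*Protocol article*

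**What the plan says.** The protocol article's Trial objectives section gives the MRI substudy the aim "to provide an explanatory mechanism for associated symptom change by examining whether MTX reduces synovitis, and whether this is related to symptom change". The Discussion paragraph of the abstract repeats the second half: "The MRI substudy will address the relationship between synovitis and symptom change".

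The MRI analyses are set out at the end of the Primary endpoint analysis section, which states that "Analysis of MRI endpoints will be exploratory" and then assigns three methods:

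- Effect of treatment on MRI features: "Treatment groups will be compared with respect to changes in synovitis, cartilage and bone using linear regression models", adjusted for the covariates of the primary analysis.
- Baseline MRI: "Linear regression models will also be used to explore the association between symptom outcome and baseline MRI measurements".
- Change against change: "Changes in MR features and the relationship of these changes with symptom changes will be explored descriptively".

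Earlier in the same section, the primary model adjusts for a baseline measure without saying whether this means baseline pain or, for other outcomes, the baseline of each. The Concomitant medication section adds days of chronic NSAID and opioid use as a covariate. The Statistical analysis section leaves full detail to a separate analysis plan, which is not at hand.

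**The concern.** Two things do not fit together.

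First, the change-against-change relation is half of the stated MRI objective, yet it is the only one of the three MRI analyses with no model. A model goes instead to baseline MRI and symptom outcome, which the MRI objective does not ask about. Description gives no estimate of the association that holds treatment arm fixed. Without one, the substudy can show two movements side by side but says little about whether they go together within an arm.

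Second, the MRI change models are specified "using linear regression models with adjustment for the same covariates as the primary analysis". The primary outcome is knee pain, so read literally synovitis change is adjusted for baseline pain and not for baseline synovitis. Baseline synovitis is the natural covariate and is already measured, since MRI is done at baseline and six months. What is at stake is precision in an optional substudy that may be well below the trial's full size.

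**Working it through.** **1. The plan's own figures.** The only sample size given is for the main trial: a difference of 2, SD 4, 80% power, 5% significance. The two-sided normal approximation gives 63 per arm and the t-test 63.77, so 64; 64/0.8 = 80 per arm, or 160 in total. This reproduces and does not bear on the point. No size is given for the MRI substudy. If everyone joined and 20% were lost, it would have 160 × 0.8 = 128 completers.

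**2. Objective against analysis.**

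- Does methotrexate reduce synovitis? Analysis: randomised between-arm regression. Matched.
- Is this related to symptom change? Analysis: description. No model or estimate.
- Is baseline MRI associated with symptom outcome? Analysis: regression. Not part of the MRI objective.

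**3. What pooling would do.** The text does not say whether the description is by arm, so this is conditional. Assume 1:1 allocation, within-arm SDs of 1, treatment shifts of d in synovitis and 0.5 in pain, and no within-arm link. The pooled covariance is d × 0.5/4, and the pooled variances are 1 + d²/4 and 1 + 0.5²/4 = 1.0625.

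- d = 0.5: 0.0625/1.0625 = 0.059.
- d = 0.8: 0.100/√(1.16 × 1.0625) = 0.090.

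The within-arm value is 0. The distortion is small, but it points towards the hypothesis, and an arm term removes it.

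**4. Precision of the association.** By Fisher's transformation, tanh(atanh(0.3) ± 1.96/√(n−3)), an observed correlation of 0.3 has these 95% intervals at assumed numbers of completers:

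- n = 40: −0.01 to 0.56.
- n = 80: 0.09 to 0.49.
- n = 128: 0.13 to 0.45.

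**5. Own-baseline adjustment.** Assume equal variance s² at both visits and correlation r between them. The variance of change is 2s²(1−r). The residual variance after adjusting for own baseline is s²(1−r²). The ratio is (1+r)/2, so the reduction is (1−r)/2.

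| Assumed r | 2(1−r) | 1−r² | Ratio | Reduction | SE ratio |
|---|---|---|---|---|---|
| 0.3 | 1.40 | 0.91 | 0.65 | 35% | 0.81 |
| 0.5 | 1.00 | 0.75 | 0.75 | 25% | 0.87 |
| 0.7 | 0.60 | 0.51 | 0.85 | 15% | 0.92 |
| 0.9 | 0.20 | 0.19 | 0.95 | 5% | 0.97 |

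Adjusting for baseline pain recovers part of this. If baseline pain relates to synovitis change only through baseline synovitis, the part recovered is the squared pain-synovitis correlation: 0.3² = 9% of the gain at an assumed 0.3.

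**The case against.** The strongest reply is that the MRI work is optional, labelled exploratory and of unstated size, and that detail is deferred to the analysis plan. Description is then a modest and honest choice: with 40 completers even a correlation of 0.3 would have an interval touching zero. Nothing in the text says the arms will be pooled, and a descriptive account can include within-arm plots and correlations. All of this is fair. It lowers the weight of the point and does not remove it: the article is not silent here but names a method for each MRI analysis, and the method named for this one yields less than the objective sets out to examine. The exploratory label limits how strongly a result may be read; it does not rule out an estimate with an interval.

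On covariates, the reply is that a baseline measure, carried over to another outcome, can naturally mean that outcome's own baseline. The SF-12 scores are to be analysed by the primary outcome's methods, which fits that template reading. On it, no precision is lost. This stands as one of two readings, so the wording is ambiguous and not shown to be an error.

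A reader might also infer three stronger points that the documents do not support:

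- **That the plan must estimate how much of the pain effect runs through synovitis.** The objective asks only whether the changes are related. An indirect effect would be hard to defend here: synovitis and pain change are measured over the same interval, and the Concomitant medication section permits analgesic increases and some corticosteroid use after randomisation, which could influence both.
- **That the baseline MRI model lacks a treatment interaction.** Predicting response from baseline is an aim of the biological substudy alone.
- **That field strength must be a covariate.** That is detail for the analysis plan, and allocation is 1:1 within sites.

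**Conclusion.** The point holds in a limited form. The article fixes description as the method for half of the MRI objective, and this gives no arm-adjusted estimate of the association between synovitis change and symptom change. It would be wrong to say that the MRI objective goes unanswered: whether methotrexate reduces synovitis gets a valid randomised comparison. Any distortion from pooling is conditional on pooling and small, 0.06 to 0.09 under the assumed shifts.

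The covariate wording needs settling. If own baseline would otherwise be omitted, and variances are equal at both visits, the avoidable variance is 5% to 35% for assumed r from 0.9 down to 0.3, slightly less if baseline pain is in the model. If own baseline was always meant, the loss is zero. The values of r are assumptions; the documents give none. Either way the issue is precision: under randomisation the comparison remains valid. The primary pain analysis is not affected.

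**What to change.** Two changes of wording, made before any data analysis.

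1. In the MRI paragraph of the Primary endpoint analysis section, add an exploratory linear regression of six-month NRS pain on change in synovitis, with treatment arm, baseline NRS and baseline synovitis as covariates. Report the coefficient for synovitis change with a confidence interval. State that it is an association, not a proportion of the treatment effect explained. Because baseline NRS is in the model, this coefficient is the same whether the outcome is six-month pain or change in pain. Descriptive displays can stay alongside.

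2. Replace the reference to the primary analysis's covariates by a statement that each continuous MRI and secondary outcome is adjusted for its own baseline value where one is collected. The qualifier is needed because Table 2 shows that some items, such as global improvement, have no baseline.

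The cost is a few lines of text and one extra model on data already being collected. The downsides are wide intervals in an optional substudy and possible confounding by analgesic or steroid use after randomisation. Both should be stated with the result.

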### Health economics analysis

An economic analysis will be undertaken in order to determine the cost-effectiveness of oral MTX for the treatment of knee OA. A cost-utility analysis will also be undertaken to explore the impact on health-related quality of life. The analyses will be conducted from the perspective of the United Kingdom NHS and Personal Social Services (PSS), in line with National Institute for Health and Care Excellence recommendations [58].

Health benefits for the economic evaluation will be measured in terms of pain reduction and QALYs. The QALY is a generic outcome which enables decision makers to compare across different disease areas. QALYs will be generated from the EuroQol EQ-5D-5 L for use in the cost-utility analysis, and will be estimated by measuring the area under the curve [59]. Utility data will be collected at the same time points as for clinical outcomes (at baseline, six months and 12 months).

Costs of the intervention, control and the total health care costs during the treatment and follow-up period will be assessed, including costs of adverse events and medications. Health service resource use will be collected via a self-reported resource use questionnaire, with national costs applied to the quantities of resources utilized, for example using NHS Reference Costs [60] and Unit Costs of Health and Social Care [61]. The unit costs of medications will be sourced from the British National Formulary [62].

The within-trial analysis will use regression methods to allow for the correlation between cost and outcome data generated from the trial, with adjustment for covariates. A cost-effectiveness analysis will determine the cost per unit of reduction in knee pain score (as measured on the NRS). A cost-utility analysis will be undertaken to generate the cost per QALY. The results will be presented in terms of incremental cost-effectiveness ratios (ICERs). Future costs and outcomes will not be discounted due to the trial follow-up being one year. Cost-effectiveness acceptability curves will be produced to explore the probability that MTX will be cost-effective at different cost-effectiveness thresholds [63].

## Discussion

Current medical therapy does not provide satisfactory pain relief in the majority of people with OA [64]; with the rapidly ageing population the prevalence of OA will continue to rise over the next decade. Unless the barriers to successful treatment of OA are overcome, the already considerable social and economic burden will soon reach an unsustainable level. The last decade has seen major advances in understanding OA pathology. MRI has demonstrated that synovial inflammation is common in OA and is related to symptoms. MTX is the most common agent used to treat synovitis in RA and because of its favourable efficacy, long-term retention rates, low cost and established track record it has become the standard by which other DMARDs are evaluated, supporting our choice to use MTX rather than any other DMARD for a trial in OA. Since the design of this study and conduct of the systematic literature review, a single-centre randomized controlled trial of MTX in knee OA has been published [65]. The study demonstrated a clinically relevant reduction in knee pain and physical function in the intervention group compared with the placebo group at 28 weeks. A significantly higher proportion of patients in the MTX group (53%) showed a reduction in VAS of more than 20 mm compared to the placebo group (24%; *P* = 0.018). The positive findings of this study reinforce the potential of MTX as a treatment for OA. However, given the substantial impact that using MTX for treating OA would have on clinical practice, a large multi-centre confirmatory study is essential. The PROMOTE trial has been designed to be pragmatic in nature so as to answer the question as to whether MTX is a valuable addition to the overall management of patients with OA.

## Trial status

Recruitment to the trial began in June 2014. Follow-up of participants is in progress and is expected to be completed in December 2016.

## Abbreviations

AICAR: Aminoimidazole carboxamide ribonucleotide
ALT: Alanine aminotransferase
CCG: Clinical Commissioning Group
CCP: Cyclic citrullinated protein
CCRN: Comprehensive Clinical Research Network
CPPD: Calcium pyrophosphate crystal disease
CRF: Case report form
CRP: C-reactive protein
CVD: Cardiovascular disease
DMARD: Disease modifying anti-rheumatic drug
eGFR: Estimated glomerular filtration rate
FBC: Full blood count
GP: General practitioner
HADS: Hospital Anxiety and Depression Scale
IA: Intra-articular
ICER: Incremental cost-effectiveness ratio
ICOAP: Intermittent and Constant Osteoarthritis Pain
IL: Interleukin
LFT: Liver function test
LTF: Lateral tibiofemoral
MHRA: Medicines and Healthcare Products Regulatory Agency
MOAKS: MRI Osteoarthritis Knee Score
MRI: Magnetic resonance imaging
MTF: Medial tibiofemoral
MTX: Methotrexate
NHS: National Health Service
NICE: National Institute for Health and Care Excellence
NIMP: Non-Investigational Medicinal Product
NRS: Numerical rating scale
NSAID: Non-steroidal anti-inflammatory drug
OA: Osteoarthritis
OA QoL: Osteoarthritis Quality of Life Scale
PF: Patellofemoral
PICS: Patient Identification Centres
PsA: Psoriatic arthritis
PSS: Personal Social Services
QALY: Quality-adjusted life year
RA: Rheumatoid arthritis
RF: Rheumatoid factor
SD: Standard deviation
TNF: Tumour necrosis factor
U&E: Urea and electrolytes
ULN: Upper limit of normal
VAS: Visual analogue scale
WCC: White cell count
WOMAC: Western Ontario and McMaster Universities Index of OA
